| --- |

| Project objectives and finalities |
| --- |
| **1/ Detailed objectives, with figures whenever possible**  **Principal objective:**  The main research objective is to assess the effect of two modalities of organised CC screening programmes on CC screening uptake: 1) combining sending invitation letters to non-adherent women with sending GPs a list of their non-adherent patients (optimised cancer screening group), 2) sending invitation letters to non-adherent women only (standard cancer screening group), compared to 3) no intervention (usual care group).  In view of the previous literature (13,14,15,16), the increase in screening uptake could reach 25% and 15% in the optimised and standard cancer screening groups respectively. The number of eligible patients identified (n= 94 393; 2020) should be sufficient to show a difference between the “optimised screening” and the “standard screening” arms. On the basis of an initial screening uptake of 61.3% in the general population in the third arm ("usual care"), increased participation could thus reach an absolute value of (1–0.61) × 25% in arm 1 and (1–0.61) × 15% in arm 2, corresponding to 9.7% and 5.8% respectively. Calculation of the NNT for the present study is included in the statistics section*. 2. Statistical justification of the number of inclusions.*  **Secondary objectives:**  *Description of the types of tests carried out in first intention and the results of these tests in the 6 months after intervention.*  The first secondary objective is to describe the types of tests carried out and the test results 6 months after the intervention. In 2020, the health authorities recommended an HPV test rather than a cervical-uterine smear test for women aged 30 to 65. In this context, the secondary judgement criteria will be the proportion of cytology examinations carried out among all tests performed, the proportion of HPV tests carried out among all tests performed, and the proportion of tests yielding abnormal results (cytology, HPV) among all tests performed.  *Description of the types of tests performed to lesions detected by screening and the results of these tests in the 12 months following the intervention.*  The second secondary objective is to describe the types of test carried out and the results from these tests in the 12 months after the intervention.  A “reflex” test is performed in second intention on the same initial screening sample following a positive or abnormal test; the result indicates the course of action to follow. In the case of a positive HPV test, the “reflex” test is cytological. In the case of abnormal cytology, the reflex test is for HPV. The associated secondary judgement criterion is the percentage of “reflex tests” conducted among the abnormal tests at 6 months.  The presence of lesions is checked for via colposcopy and confirmed by biopsy or cervical conization in cases with any abnormalities. A secondary judgement criterion will be the percentage of biopsies and conizations carried out among the abnormal screening tests in the 12 months following the intervention. The 12-month duration takes the time required for follow-up and for investigation procedures into account.  The most serious lesions are pre-cancerous lesions (neoplasia, second and third-grade cervical intraepithelial neoplasia), in-situ carcinomas and invasive cancers. A secondary judgement criterion will be the percentage of high-grade lesions detected (second, a third-grade cervical intraepithelial neoplasia, including in-situ carcinomas and cancers) among the abnormal screening tests in the 12 months following the intervention.  *Description of the treatments undergone by the women following abnormal screening tests in the 12 months after the intervention*  The third secondary objective is to describe the treatments undergone by women following abnormal screening tests in the 12 months after the intervention. The associated secondary judgement criterion will be the proportions of treatments carried out (conization, laser, hysterectomy) among the abnormal screening tests in the 12 months following the intervention.  *Description of the factors associated with lower participation in screening*  The fourth secondary objective is to describe the factors associated with lower screening test uptake.  Many studies have reported the existence of social inequalities in screening (2). Certain factors have been put forward: educational level, income, socio-professional category, comorbidities and age (2).  *Description of the healthcare trajectory of women undergoing a screening test.*  The fifth secondary objective is to describe the healthcare trajectories of women undergoing a screening test.  One issue will be to determine which type of care provider women will contact for a screening test. The caregivers who perform screening tests can be GPs, midwives or gynaecologists, and we will therefore analyse the proportion of women who resort to a GP, a midwife or a gynaecologist to undergo their screening test. The time required for women to resort to screening after having received the invitation to do so will also be determined. This time lapse will correspond to the time required to make an appointment and how easy it is to obtain an appointment with the professionals they contact. The judgement criterion will be the time between posting the letter and the date of the screening test.  **2/ Qualitative aspects targeted**  /  **3/ Expected benefits**  The first expected benefit is an increase in participation rates in screening tests by about 20% in the arm with a list sent to GPs and by about 15% in the arm with only the letter to the patient.  The increase in participation will enable the detection of pathological lesions to be improved: 5% for pathological smear tests and 10% for oncogenic HPV tests. The expected gynaecological monitoring is over 90% with follow-up or adequate treatment of high-grade lesions,  Our study is in complete coherence with the 2019-2024 Cancer Plan, and the authors of this project believe that an increase in screening participation will yield benefits in terms of morbidity and mortality in the target population.  **4/ Future perspectives for the project: shared action, larger-scale deployment or deployment on national level, publications planned ….**  The deployment of organised screening over the whole national territory in 2020 should enable an increase in the proportion of women having undergone a screening test in the last 3 years. Our study sets out to complement this screening system by providing GPs with a practical guidance tool. As non-adherence is multi-factorial, the fact of giving GPs a list of non-adherent women should help increase the efficacy of the letters sent to patients in the organised screening framework.  The present study is based on a simple and fairly inexpensive design, so that a generalisation of the suggested intervention will be feasible if the effects prove positive.    The present study combines the benefits of a systematic approach coordinated by an impersonal structure (the CRDC) and the benefits of an approach centred on patients and supported by their GP. Our study proposes an intervention that capitalises on the special position occupied by GPs towards their patients. Our intervention reinstates their position in the screening process, in coherence with the expectations expressed in previous research. |

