
| Project implementation |
| --- |

| **METHODOLOGY**  **General aspects**  This will be an open, prospective, randomised controlled trial with three parallel arms.  The study will concern all GPs in the Loire-Atlantique *département*, France applying the inclusion and non-inclusion criteria, and their female patients aged from 40 to 65 years who are eligible for cervical cancer screening.  The randomisation unit will be the medical practice, identified by its address. Randomisation will thus be performed on the place of practice rather than the practitioner to avoid confusion bias between arms. Thus several practitioners practising in a given place of practice will be assigned to the same arm, either "List to GP + letter to patients", "letter to patients alone", or "screening on individual initiative ".  The statistical unit will be the patient.  The analysis will be intention-to-treat. The study will be conducted in "real life" conditions taking account (and reporting on) of the fact that a given intervention has variable impact depending on the practitioners targeted by the intervention.  **Study population**  Inclusion criteria  The GPs eligible for this study will be individuals who do not have *Mode d'Exercice Particulier* status (complementary and alternative medicine), practising in Loire Atlantique. The list of the GPs in this territory will be derived from CRCDC Pays de Loire (cancer screening coordination centre). The population of eligible GPs is estimated to amount to 1500.  Eligible patients will have the following characteristics:  - Age 40 to 65  - Affiliated to a health insurance system  - Present on the list of a participating GP  - Residing in Loire Atlantique.  In practice, the list of patients will be derived from CRCDC Pays de Loire; their database collects information from the different health insurance bodies (*Régime Général, Mutualité Sociale Agricole*, other).  In Loire Atlantique the target population was estimated in 2019 to amount to 233 500 women (French public health data).  Non-inclusion and exclusion criteria  The GPs will receive information on the implementation of the survey 3 months before it starts, and will be able to contact the CRCDC data protection delegate if they wish to refuse to participate. The GPs who refuse to participate will not be included and thus will not be assigned to any arm in the process of randomisation (see also section on ethics and non-opposition).  Patients with a history of total hysterectomy and those with a pathological smear result will not be eligible for screening and excluded.  Women who have not named an attendant GP (*médecin traitant*) will not be included. In Loire-Atlantique the percentage of insured individuals who have not named their attendant GP has been estimated to be between 7 and 15% on the basis of health insurance data, the figure being variable from one territory to another. The percentage specifically aggregating the population of women aged 40 to 65 years is not available).  **Randomisation, intervention arms and control arm**  Randomisation will concern medical practices, so that practitioners will be distributed across the three arms.  On the basis of the list of practitioners assigned to the different arms, the CRCDC will draw up a list of names of women eligible for cervical screening aged 40 to 65 for each GP, excluding patients meeting non-inclusion criteria.  Thus when randomisation is complete, participating GPs and their patients will be randomly assigned to one of the three following arms:  "optimised cancer screening" group  • The GPs will receive a list of their patients aged 40 to 65 who have not undergone cervical cancer screening in the last three years, with specific attention to factors of non-participation.  • The patients will receive a letter: 1) inviting them to obtain an appointment with a health professional (GP, midwife, gynaecologist) to undergo a screening test, and 2) specifying that the screening procedure cost will be covered 100%.  "standard cancer screening" group  • The GPs in this arm will not receive the list of their patients aged 40-65 who have not undergone cervical cancer screening in the last three years.  • The patients will receive a letter: 1) inviting them to obtain an appointment with a health professional (GP, midwife, gynaecologist) to undergo a screening test, and 2) specifying that the screening procedure cost will be covered 100%.  "usual care" group  • The GPs in this arm will not receive the list of their patients aged 40-65 who have not undergone cervical cancer screening in the last three years.  • The patients will not receive a letter from CRCDC. The consultation and the test will be reimbursed as normal by the health insurance system and the complementary insurance.  **NB** The patients aged 40-65 who have not undergone cervical cancer screening in the last three years will be identified by way of the absence of health insurance reimbursement for the intervention.  In practice, the list of patients will be derived from the Pays de Loire CRCDC database, which draws its information from the health insurance bodies (*Régime Général, Mutualité Sociale Agricole*, other).  For Loire-Atlantique, the number of patients aged 40 to 65 who have not undergone a cervical smear test in the last three years was estimated in 2019 to be 130 300 (public health data).  **Main and secondary judgement criteria**  A. **The primary endpoint** is the proportion of women aged 40 to 65 who are up-to-date with their screening (having performed a screening test in the last 3 years) 6 months after the intervention. The 6-month duration takes into account the capacities of professionals to respond to a consultation request for this type of medical procedure.  **B. Secondary judgement criterion**  - the proportion of cytology examinations carried out among all tests performed, the proportion of HPV tests carried out among all tests performed, and the proportion of tests yielding abnormal results (cytology, HPV) among all tests performed.  - the percentage of “reflex tests” conducted among abnormal tests at 6 months.  - the percentage of biopsies and conizations carried out among the abnormal screening tests in the 12 months following the intervention.  - the percentage of high-grade lesions detected (second, a third-grade cervical intraepithelial neoplasia, including in situ carcinomas and cancers) among the abnormal screening tests in the 12 months following the intervention.  - the rate of treatments carried out (conization, laser, hysterectomy) among the abnormal screening tests in the 12 months following the intervention.  - Participation rate according to age (over 50), income (women with low incomes qualifying for basic health coverage) and comorbidities.  - the proportion of women having consulted a GP, a midwife or a gynaecologist for a screening test.  - the time period between posting the letter and the date of the screening test.  **Data collection**  The data will be collected or extracted via complementary, coordinated means:  **• Some of the data will be collected from CRCDC** via routine methods:  - Identification of patients eligible for organised screening who have named an attending GP meeting the inclusion criteria for GPs  - Patients having undergone screening or an HPV test (date of the examination in this case) in the 12 months following inclusion.  - Patient's address and IRIS code so as to attribute a European Deprivation Index score.  The study will process data transferred between the health insurance body and CRCDC as defined in the national references: "Types and contents of files required for the creation of databases for cervical cancer screening" (INCa September 2018).  Administrative and socio-demographic data enabling the characterisation of the women:  • Family name • Given name(s) • Date of birth (DD/MM/YYYY) • Address • Post code, town • Health insurance body • Email • Named attending GP • Identification number of the named practitioner • Universal health cover status (CMU) (yes/no).  Variables enabling identification, for each woman, of the medical acts performed in the setting of cervical cancer screening:  • Date of the act • Code of the act • Identification number of the practitioner performing the act • Identification number of the prescribing practitioner   - Data specifically collected from the health insurance system:   . Characteristics of the GPs: age, gender, classification of the practice locality, activity in numbers of acts per year, convention sector (1,2), practising alone or in a group  . Patient characteristics: CMU status, long-term illness (ALD) and CS status (assistance in contracting a complementary health insurance) (with a view to adjusting analyses of these variables).  . Number of consultations with a GP/ gynaecologist a) in the 24 months before the dispatch of the invitation letter and b) in the 12 months following the dispatch of the letter.  **Statistical analysis**  **1. Description of the statistical methods planned**  All the data will be described globally and per randomisation arm. The statistical unit will be the woman eligible for screening. The significance threshold will be set at 5%.  The analyses will be performed using R 3.6.0. software (R Foundation for Statistical Computing, Vienna, Austria. URL <https://www.R-project.org/>.)  **Main criterion**  The percentage of women up-to-date with their screening 6 months after the intervention will be compared across arms using a generalised mixed linear model to adjust the analysis on the random effect of the GP.  A hierarchical procedure will be used to successively test the comparisons of the three arms, controlling for type I error.  The first hypothesis tested will be the difference between the intervention arms (“optimised organised cancer screening” and “standard organised cancer screening”) and the "usual care" arm. If the result is significant, a second test will be conducted, comparing the "optimised screening" arm with the "standard screening" arm.  **Exploratory secondary analyses**  The types of tests conducted and the types of professional consulted will be described and compared between arms using the same models as for the main criterion. The time-lapse to screening uptake will be described and compared using a mixed Cox model adjusted for the type of professional chosen, the randomisation arm and the GP as a random effect. The percentages of cytology tests and HPV tests conducted in the following 6 months and the percentage of abnormal tests among all the screening tests will be calculated and compared between the different arms using a generalised mixed linear model adjusted on the GP. The same will apply to the percentage of "reflex tests" conducted among the abnormal tests at 6 months, to the percentages of biopsies and conizations carried out among the abnormal tests in the ensuing 12 months, to the percentage of high-grade lesions detected (second- and third-grade cervical intraepithelial neoplasia, including in situ carcinomas and cancers) among the abnormal screening tests in the ensuing 12 months and to the percentages of women resorting to each type of professional.  A generalised mixed linear model will be used to assess factors associated with screening uptake among the following: age of the woman; low economic status; long-term illness status; the French DEPrivation index of the place of residence; and the number of visits to GPs, midwives or gynaecologists during the follow-up period.  **2. Statistical justification of the sample size**  Over the 2017-2019 period, the screening participation rate in Loire-Atlantique was 61.3% and concerned approximately 154 000 women (internal source: regional organisation in charge of cancer screening). On the basis of data from the literature, the research team estimates that the proportion of women who will undergo a screening test while not having had a smear test for over 3 years could reach 25%, thanks to the letter sent to their GP that includes the list of his or her non–up-to-date patients ("optimised" arm), whereas the increase in participation should be more limited in the "standard screening" arm (15%) and nil in the "usual care" arm. After the intervention, participation rates should therefore be 71% in the "optimised screening" arm, 67.1% in the "standard screening" arm and 61.3% in the "usual care" arm.  In September 2020, there were 1 395 GPs in the Loire-Atlantique, with an average of 2.15 GPs per medical practice. The multiplication factor derived from the cluster randomisation is defined at 12.8 (intra-class correlation coefficient: 0.05). Inclusion should reach a minimum of 37 776 patients per arm to demonstrate a difference between the "optimised" arm and the "standard" arm. As a total of 154 000 eligible women will be included in the study, we will be able to demonstrate this difference with 51 300 women per arm.  **3. Randomisation**  The practices of the GPs will be randomised in the three parallel arms (cluster randomisation) with a 1:1:1 ratio. Each GP will be linked to the randomisation arm and his or her place of practice, and each patient to the randomisation arm of her attending GP.  **Piloting of the project and the roles of the different players**  **Steering Committee**  The project will be coordinated by [name].  [name] [name] is the project deputy coordinator.  The collective expertise is ensured by the Steering Committee which will gather all the partners  This Committee will define the general organisation and deployment of the project, will coordinate information and will decide on how to proceed in case of unexpected events.   - [name], project coordinator for Nantes University - [name], deputy project director, for CRCDC Pays de la Loire - [name], in charge of statistical studies, for the health insurance body   **Roles of the different people involved**  Department of general medicine  Throughout the study, the coordination will be ensured by [name] (Nantes University, INSERM U 1232, team 2). He will be in charge of the design and drafting of the final protocol for the randomised trial, the drafting of intermediate reports and the final scientific report, and of the scientific valorisation of the trial.  CRCDC  CRCDC represented by [name] will ensure the study coordination.  It will take part in all stages in the research, from the design of the protocol for the randomised trial to its final scientific valorisation. It will be in charge of collecting information from the different sources, and of dispatch of the letters to the eligible women and the GPs. It will have the task of updating the status of each patient with respect to organised cervical cancer screening. The CRCDC will be in charge of the database. It will be in charge of the transfer of data to the research teams.  The Nantes CHU (university hospital) clinical research directorate (DRC)  The Nantes CHU DRC methodologist and biostatistician will ensure that the methodology of the statistical analyses is complied with. She will be in charge of drawing up the randomisation list, of the analysis of all the data from the randomised trial using the anonymised data transferred by CRCDC.  The DRC teams will be in charge of legal procedures and requirements.  Health Insurance bodies  As in the IDLN study ([15,29] a partnership will be established with the health insurance bodies.  They will provide the CRCDC with the data that is routinely transferred, and will also include certain data specifically collected in the setting of the present study (see Data Collection section)  The health insurance bodies will provide their expertise in the identification of medical acts and the tracing of healthcare trajectories using information in their databases.  **Legal requirements, ethics committee and non-opposition by participants**  The Jardé legislation does not apply to this study. The research does not involve human beings directly, since it aims to evaluate modes of practice among health professionals.  1. Computerised data and CNIL approval  The data processing will be registered in the Nantes CHU data protection body (RGPD).  The data collected in the course of the study will be stored in a computerised file in compliance with the "informatique et libertés" legislation of January 6th 1978, modified by legislation n° 201#8-493 dated 20th June 2018 relating o the protection of personal data, and with the European parliament legislation 2016/679 and that of the European Council dated 27th April 2016 relating to the protection of individuals with respect to the processing of personal data and the free circulation of that data.  The protocol belongs to the field of methodology (reference MROO4 with which Nantes CHU complies.)  2. Ethics approval  The experimental protocol will be evaluated in view of the ethical requirements. The study does not come under Jardé[[1]](#footnote-2) requirements. The project will be submitted to prior approval by the Ethics Committee assessing non-RIPH projects like that of the Collège National des Généralistes Enseignants (CNGE).  3. The principle of non-opposition in the setting of a study aiming top assess new procedures in public health.[[2]](#footnote-3)  At least 3 months before the first inclusion, the GPs will be informed by letter about this pilot study on cervical cancer screening. They will be invited to signal their refusal if they do not wish to participate. In the absence of explicit refusal by a GP, he or she will be included in the study.  This mode of collection of non-opposition will be conducted in compliance with international ethical requirements for studies aiming to assess new procedures in the area of public health. International recommendations stipulate that explicit consent can be waived when the study concerned meets the following: 1) The research is designed to evaluate possible changes in public health programmes, and 2) The research cannot practicably be carried out without the waiver.  The mode of implementation will follow that agreed by CNIL, CPP and various international players (clinicaltrials.gov, JAMA) for the IDLN study previously funded by the National Cancer Institute (France)  **Data collection and anonymity**  CRCDC- Pays de la Loire will collect the study data.  Initially, the CRCDC Pays de Loire computing department (ZEUS database) will be in charge of the request to form the populations for the three arms.  The data will be centralised by CRDCDC.  The methods of transfer of data between the health insurance and the regional cancer screening coordination centre will be those in routine use.  CRCDC will transfer an anomymised database comprising a patient identifier code, but no data identifying the person, to the person in charge of the analysis (dates replaced by periods)  **Data collection - quality control**  CRCDC will collect data over the 12 months following the intervention.  CRCDC- Pays de la Loire will produce the data described above, drawing on the data transferred by the health insurance.  **Management and analysis of the data and valorisation**  The data analysis will be conducted under the responsibility of the study methodologist and biostatistician, on a database transferred by CRCDC. The valorisation of the results will be conducted via collaboration among the individuals involved in the study, commensurately with their implication and responsibilities at the different stages.  **Project implementation calendar**  **Provisional calendar**  The project is planned to run over 36 months.  **M-4** **to M-2:**  - Legal procedures, registration of the study in Nantes CHU RGPD register, submission of the project to the ethics committee, registration of the trial on clinicaltrials.gov.  - The health insurance body transfers to CRCDC the list of non-MEP GPs practising in Loire Atlantique (this information circuit is already established between the health insurance bodies and CRCDC).  - Transfer to CRCDC by the different health insurance bodies of information relating to women aged 40 to 65 residing in Loire Atlantique (this information circuit is already established between the health insurance bodies and CRCDC):  . Name, first name, date of birth, Social Security number, address of place of residence (data that is routinely transferred), name of GP  . Presence of a medical act enabling identification of a cervical cancer screening test (according to standard codes) in the course f the last 3 years  . ALD (long illness), CMU (universal health cover) and ACS (complementary health cover allowance) status.  **M-2 à M-0**:  - CRCDC generates an inclusion code per medical practice and transfers the coded list to the methodologist and statistician.  -The methodologist statistician carries out the centralised randomisation of the addresses of places of practice of GPs to 3 parallel arms, and transfers the result of the randomisation to CRCDC. This procedure avoids the transfer of names attached to data to the coordinator's team. The name-linked data remains with CRCDC, as is usual with respect to CNIL requirements.  **M0-M2**: Intervention in arms 1 and 2:  In the arm "lists to GPs AND letter to patients"  . For patients not having undergone cervical smear in the last 3 years dispatch of the letter inviting them to undergo a screening test covered 100% by the health insurance  AND  . Parallel dispatch to each GP of a list of the names of their patients who have not undergone a smear test in the last 3 years  In the arm "Letter to patients":  . For patients not having undergone cervical smear in the last 3 years dispatch of the letter inviting them to undergo a screening test covered 100% by the health insurance  No list of patients is however sent to the GPs.  In the arm "Individual screening initiative ":  . No letter is sent to women who have not undergone a screening test in the last 3 years  . No patient lists are sent to the GPs.  **M10**: Closure of the database relating to follow-up data for the main criterion (occurrence of a screening test)  **M10 to M12: Analysis of the main judgement criterion – intermediate report on participation**  **M20**: Closure of the database relating to anatomo-pathological data and other secondary criteria. Transfer by CRCDC to the coordinator of a file with anonymous individual data relating to participating patients.  **M20 to M26**: **Analysis of the secondary criteria** concerning anatomo-pathological data, the care trajectory, and factors associated with lesser participation.  **M26 to M29:** Drafting of the final report  **M29 to M32:** Drafting of scientific articles and follow-up to publication   | **Actions** | **M-4 to M-2** | **M-2 to M-0** | **M0 to M2** | **M10** | **M10 to M12** | **M20** | **M20 to M26** | **M26 to M29** | **M29 to M32** | | --- | --- | --- | --- | --- | --- | --- | --- | --- | --- | | Legal procedures | X |  |  |  |  |  |  |  |  | | Identification of eligible women by CRCDC | X |  |  |  |  |  |  |  |  | | **Randomisation** of GPs to 3 parallel arms |  | X |  |  |  |  |  |  |  | | **Intervention**: dispatch of letters in arms 1 and 2 |  |  | X |  |  |  |  |  |  | | Closure of database for main criterion |  |  |  | X |  |  |  |  |  | | **Analysis of main criterion** |  |  |  |  | X |  |  |  |  | | Closure of database for secondary criteria |  |  |  |  |  | X |  |  |  | | **Analysis of secondary criteria** |  |  |  |  |  |  | X |  |  | | Drafting final report |  |  |  |  |  |  |  | X |  | | Scientific valorisation |  |  |  |  |  |  |  |  | X | |

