| **1/ Expected results**  Our study should lead to an increase in uptake of organised cervical cancer screening as a result of sending GPs a list of their patients aged 40 to 65 who have not undergone a test in the last 3 years in comparison to 1) only sending a letter to women who are not up to date (routine in organised screening) or 2) no letter sent to GPs or their patients.  In view of the previous literature (13,14,15,16), the increase in screening uptake could reach respectively 25% and 15% in the optimised and standard organised cancer screening groups. The number of eligible patients identified (n= 94 393; 2020) should be sufficient to show a difference between the “optimised screening” and the “standard screening” arms. On the basis of an initial screening uptake of 61.3% in the general population in the third arm ("usual care"), increased participation could thus reach an absolute value of (1–0.61) × 25% in arm 1 and (1–0.61) × 15% in arm 2, corresponding to 9.7% and 5.8%, respectively. The calculation of the NNT (number needed to treat) we propose to use is set out in the section Statistics – justification of the numbers to include.  At a time when organised screening is being set up on a national scale:   - This project will provide a tool to back up practice among GPs, in the context of the decision in the national Cancer Plan to make GPs the coordinators of screening. - The project adds to the various modes of intervention available to decision-makers to increase uptake of cervical cancer screening. - This project enables the evaluation of the trajectories of women who undergo a test after receiving the letter while they have not undergone one for the last 3 years. It will enable a description of resort to care in terms of the professionals consulted and the time-lapse to access to care. - This project finds its place in the dynamic of organised screening on the scale of a regional territory (Loire Atlantique), where the participation rate is already higher than the national rate. - This project affords a unique opportunity to analyse the effects of the implementation of organised screening using a scientific method - A robust design, based on a randomised trial, unprecedented in the area of cervical cancer screening. - A study with considerable power, since the analysis concerns the whole population of a whole *département*. We found no other study on this scale in the literature. - Our project will produce results that will be reproducible, since the design is in intention to screen, and the intervention tested is straightforward and inexpensive - With respect to the research dynamic, this project will back up the dynamics of collaborative work among the main players in care strategies and screening in primary care: GPs, CRCDC, the health insurance bodies, the CHU   **2/ Method of evaluation**  The method of evaluation used will be a reference scientific method deploying a large-scale randomised trial for the main criterion. The other evaluation criteria (secondary) will be the subject of scientific analyses according to reference methods (see also the section Statistic).    The participation rate will be compared across arms using generalised linear models to take account of the cluster randomisation.  The proportion of abnormal smear results and positive HPV tests, and the time to consultation according to the professional chosen, will be described and compared across the three arms.  Factors associated with non-participation will be analysed using multivariate linear regression.   - Evaluation of the participation rates at 6 months:   Participation rate = number of screening tests (cervical smear or HPV test) / Number of patients targeted by organised screening   - Results of screening tests - Total number of cervical smears or HPV tests with results - % of unsatisfactory cervical smear tests /HPV tests - % of positive cervical smear tests /HPV tests - The screening activity per speciality will be described, reporting the number of cervical smears performed and the number of HPV tests per practitioner speciality: GP, gynaecologist, midwife, other (laboratory)     **3/ Indicators for project follow-up and for results, mode of evaluation of the quality of the action undertaken, etc**  Project follow-up indictors:  Compliance with the different stages in implementation as described in the project calendar  Results indicators:  Number of women eligible for screening  Number of letters sent to arms 1 and 2  Number of screening tests performed at 6 months  Number of abnormal test results in the 3 arms.  Evaluation of the quality of the actions undertaken  The study we propose is a large-scale randomised trial in the general population, with a robust design and very good reproducibility*.* |

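### The exploratory time-to-screening comparison has no start date in usual care, and it adjusts for a covariate known only for tested women

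*Protocol*

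**What the plan says.** The Protocol defines the endpoint twice. Under the fifth secondary objective (Project objectives and finalities): "The judgement criterion will be the time between posting the letter and the date of the screening test". In the list of secondary criteria (Main and secondary judgement criteria, B): "the time period between posting the letter and the date of the screening test".

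For the usual care group, the section on randomisation and arms says: "The patients will not receive a letter from CRCDC". The provisional calendar repeats it for that arm: "No letter is sent to women who have not undergone a screening test in the last 3 years".

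Under Statistical analysis, Exploratory secondary analyses, the time to uptake is to be "compared using a mixed Cox model adjusted for the type of professional chosen, the randomisation arm and the GP as a random effect". Under Evaluation of results, 2/ Method of evaluation, "the time to consultation according to the professional chosen, will be described and compared across the three arms".

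The type of professional comes from the record of the screening act. Data collection lists "Identification number of the practitioner performing the act", and the related secondary criterion is "the proportion of women having consulted a GP, a midwife or a gynaecologist for a screening test".

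**The concern.** There are two separate difficulties.

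- **Time origin.** A clock that starts at posting cannot start for women to whom nothing is posted. One of the three arms in the announced comparison therefore has no defined survival time.
- **Covariate.** In a time-to-event model of screening, the untested women are the censored observations. Type of professional has no value for them, because it is created by the event being modelled. The same protocol states an intention-to-treat analysis with the eligible woman as the statistical unit, and this model cannot honour that.

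At stake is how a listed secondary criterion would be read. An arm hazard ratio from this model, printed beside the primary result, could suggest that the GP list hardly affects time to screening even when it clearly raises uptake.

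**Working it through.** The protocol gives no hazard ratio, event count or power for this analysis, so there is no figure of its own to reproduce. The check sets the definitions side by side and then illustrates the size.

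**Step 1: origin.** Both definitions start at posting. Usual care has no posting. The Method of evaluation section names three arms, so the comparison cannot be read as limited to the two letter arms. No alternative start date appears anywhere. Even in the letter arms there is no single posting date, because dispatch runs from M0 to M2.

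**Step 2: covariate.** There are two ways to handle women with no professional.

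- Give them their own level (none). That level contains no events. Its coefficient runs off towards minus infinity, which in effect removes these women from the risk sets. In a simulated data set the fit failed with a singular matrix.
- Drop them. Only tested women remain, and nobody is censored. In the same data set 2,761 of 18,000 women were left.

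Either way, the arm term rests on tested women.

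**Step 3: size, all invited women.** Inputs from the sample size section: uptake among women not up to date of 25% (optimised) and 15% (standard). Assumptions added here: these are the proportions at 6 months, hazards are constant, and there is no GP random effect.

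- Hazard = −ln(1 − p)/6. Optimised: 0.2877/6 = 0.0479 per month. Standard: 0.1625/6 = 0.0271 per month.
- HR = ln(0.75)/ln(0.85) = 0.2877/0.1625 = 1.77.
- Simulation, 6,000 women per arm: 1.77 (SE of log HR 0.042). A second simulation with 20,000 per arm: 1.76.

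**Step 4: size, tested women only.** The share left out is 1 − 0.25 = 75% of invited women in the optimised arm and 1 − 0.15 = 85% in the standard arm.

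- Simulation, 6,000 per arm, adjusted for type of professional: 1.055 (SE of log HR 0.042).
- Simulation, 20,000 per arm: 1.05 (SE 0.023). A further run gave about 1.08.
- Cross-check by formula: among women tested by month 6, the hazard at time t is λ/(1 − exp(−λ(6 − t))). At t = 0 this is 0.0479/0.25 = 0.192 and 0.0271/0.15 = 0.181, a ratio of 1.06. As t approaches 6 the ratio falls to 1.00. The underlying value therefore lies between 1.00 and 1.06, and the simulated figures scatter around that range.

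**Step 5: repaired model.** With a start time given to every woman, untested women censored at 6 months and no professional covariate, the three-arm model fits. Under an assumed 5% uptake in usual care (the protocol's nil would give no events), the hazard ratios against usual care were 3.27 (standard) and 5.78 (optimised).

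**The case against.** The best counter-argument is that tested women are the intended population. The fifth objective concerns the care trajectories of women who have the test, and it explains the delay as a matter of getting an appointment. For that question type of professional is defined for everyone and is the factor of interest. The effect on uptake is already the primary endpoint, so 1.77 and 1.05 answer different questions, and the gap between them does not measure bias in access delay. The analysis is also labelled exploratory, and a statistical analysis plan may give censoring rules.

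Much of this stands. It justifies a description of delay by professional among tested women. It does not justify an arm comparison in that group, because the arms select different fractions of women into it. It also leaves usual care without a start date. A statistical analysis plan could supply one only by departing from the endpoint as the protocol defines it.

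A reader might infer two stronger things, and the protocol supports neither:

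- **That no Cox model can be fitted.** A model limited to tested women in the two letter arms will run. What cannot be carried out is the three-arm comparison in all eligible women.
- **That the arm effect vanishes by construction.** Only the uptake component is removed. In an illustrative simulation with the same 25% and 15% uptake, tested women in the optimised arm came earlier (median about 1.7 against 2.8 months). The tested-only HR was then 1.57 (SE of log HR 0.023). The model can detect a difference in speed, but it cannot attribute that difference to randomisation.

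**Conclusion.** The concern holds in a limited form: the time-to-screening analysis is internally inconsistent as written. Usual care has no time origin although three arms are to be compared. The professional covariate confines the model to tested women, so its arm term is a non-randomised comparison of speed among them.

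On the protocol's uptake figures the difference is between an HR of about 1.77 in all invited women and about 1.05 to 1.08 in simulated tested women. The contrast is an illustration. It depends on constant hazards, a 6-month horizon (the protocol collects test dates over 12 months and fixes no horizon for this model) and omission of the GP random effect.

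The primary analysis is untouched, and nothing confirmatory depends on this endpoint. It is still a listed secondary criterion with a stated between-arm test, and is worth correcting.

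**What to change.** **Arm comparison.**

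- Assign each practice a dispatch date at randomisation, with a pseudo-dispatch date for usual care practices, and use it as time zero in all three arms. Taking M0 for everyone is less good, because dispatch over M0 to M2 could add up to two months to a woman's delay.
- Include all women not up to date at that date, and censor untested women at a stated end of follow-up.
- Keep arm and the cluster random effect, and remove type of professional.
- Have the screening coordination centre (CRCDC) compute the interval before it converts dates to periods in the file sent to the statistician. Otherwise the interval may not be recoverable.

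**Access question.** Report letter-to-test delay by type of professional as a description among tested women in the two letter arms. Cumulative incidence of a test by type of professional and arm can be added as an option. It mixes uptake with delay, so it does not replace that description.

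**Cost.** Rewording one endpoint and one model, and one assigned date per practice. No new data are needed, but the date must be set before the analysis file is built.
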